#### Secondary outcomes

The secondary outcomes include self-reported sitting time, musculoskeletal symptoms, and workability. Self-reported sitting time will be established using the Occupational Sitting and Physical Activity Questionnaire
[30] and the Workforce Sitting Questionnaire
[31]. Both the Occupational Sitting and Physical Activity Questionnaire and Workforce Sitting Questionnaire are acceptable self-report measures for assessment of sitting time at work. The Occupational Sitting and Physical Activity Questionnaire has high test-retest reliability
[30], and both questionnaires correlate well with accelerometry measures of physical activity and sedentary time making them suitable tools for this study
[30,31]. The 7-day prevalence of musculoskeletal symptoms will be recorded using the Nordic Musculoskeletal Questionnaire
[32]. Self-reported work ability will be measured by the Work Ability Index
[33]. These instruments have acceptable reliability and validity
[34-36], and measures will be recorded at baseline and 4-week follow-up.

Potential adverse effects of the interventions will be recorded at 4-week follow-up. Participants will be asked to recall if they experienced any adverse effects that they related to their involvement in the study from a list that includes: neck pain, headache, back pain, other muscle or joint pain, fatigue, loss of concentration, and work productivity.

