### Interventions

Participants will be randomly allocated to one of three study groups.

In the education intervention group, participants will receive an education package based on the 'Happy Body at Work’ program developed by a health promotion expert and physiotherapist ([name]). The education package was specifically designed for the participants in this study in consultation with the program author. It incorporates evidence-based principles of optimal seated posture, advice concerning regular postural change between sitting and standing, and physical activity guidelines for promoting a healthy lifestyle. The education package will be delivered by a researcher ([name]) who has received training in health promotion and program content from [name]. The aims of the education package are to improve the participants’ knowledge and understanding about the detrimental effects of prolonged sitting, and to motivate and engage the participants in behavior change in relation to sitting habits. The contents of the program include a multimedia presentation, a physical activity goal-setting exercise, self-monitoring of breaks from sitting, and self-monitoring of daily step count, as well as visual and auditory reminders about taking breaks from sitting.

In the sit-stand desk intervention group, participants will be provided with a WorkFit-S or WorkFit-A adjustable sit-stand workstation (Ergotron, Saint Paul, MN, USA) for a period of 4 weeks. Participants will receive the same education package as the education intervention group. Participants will also receive training in the use of the workstation by a member of the research team. Participants will set individual goals for the time that they will spend working in a standing position. Participants will be given the general advice to alternate regularly between work in a sitting and standing position, and discouraged from trying to only work in a standing position.

In the control (no intervention) group, participants will receive no information or advice about postural change and no modification to their office desk set-up. Participants in the control group will be offered the advice intervention once they have completed final data collection and they have been discharged from their involvement in the study.

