#### Randomization and blinding

Participants will be randomly allocated into one of three study groups. A researcher who is not involved in participant recruitment or data collection will produce a randomly generated sequence for allocating participants to one of the three groups. This will be done prior to commencement of the trial. This researcher will prepare consecutively numbered sealed opaque envelopes that contain the group allocation for each individual participant. The envelope for each participant will be opened after the participant has enrolled in the study and after baseline data is collected. The randomization sequence will contain equal numbers of subjects in each group but will be otherwise unrestricted.

Data collection will take place away from the participants’ office and data collectors will be instructed not to enter the office areas of participants. This will ensure blinding of the data collectors to allocation of participants to the sit-stand desk intervention group. The office set-up in the workplace setting for this trial is predominantly private, single occupier offices with few work centers using open-plan office design. This feature of the study setting will assist with limiting the exposure of participants to the other trial interventions and ensure blinding of the data collectors to treatment allocation.

Participants will be kept naive as to the main aim of the study, that is, reduction of unhealthy sitting behaviors. This is because it is believed by the research team that participants being aware that the primary outcome is to reduce sitting behavior might actually change this behavior. Participants will also be blinded where possible to the intervention groups to which they are not allocated. Knowledge of the other interventions that are being tested, both clearly being interventions designed to reduce sitting behavior, might also impact on the sitting behavior of participants. Participants will therefore be informed that they are participating in a trial of general workplace health interventions and remain blinded to the other intervention groups.

A researcher who is blinded to the participant allocation will perform data entry and analysis.

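### Adverse effects are recorded only if the participant relates them to the study, so the item gives no valid background rate from the no-intervention arm and misses unattributed harms

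*Protocol article*

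**What the plan says.** Under Secondary outcomes, the Protocol article states "Potential adverse effects of the interventions will be recorded at 4-week follow-up". It then gives the rule for what is collected: "Participants will be asked to recall if they experienced any adverse effects that they related to their involvement in the study". The list from which they recall includes "neck pain, headache, back pain, other muscle or joint pain, fatigue, loss of concentration, and work productivity". No baseline recording of this item is mentioned.

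Under Interventions, the control arm is described thus: "participants will receive no information or advice about postural change and no modification to their office desk set-up". The education arm receives an education package with goal-setting, self-monitoring and reminders. The desk arm receives the same package plus a sit-stand workstation, training in its use and individual standing goals.

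Under Randomization and blinding, all participants are treated alike as to what they know: "Participants will therefore be informed that they are participating in a trial of general workplace health interventions and remain blinded to the other intervention groups".

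The same Secondary outcomes section also provides measures that do not ask about cause: "The 7-day prevalence of musculoskeletal symptoms will be recorded using the Nordic Musculoskeletal Questionnaire", and the Work Ability Index. Both are taken at baseline and at 4 weeks, and Statistical methods lists both for the group-by-time analysis. Adverse effects do not appear in that analysis list.

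**The concern.** The listed complaints are non-specific and will have some background rate in any group of office workers. What separates that background from harm caused by an intervention is the rate in the untreated arm, collected in the same way. Here a complaint is recorded only after the participant has judged it to be linked to the study. A desk user has a new workstation, training and standing goals to link it to. An education participant has reminders and self-monitoring. A control has received neither device nor advice when the question is asked.

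Two things are at stake. First, if adverse-effect counts are set side by side by arm, lower attribution among controls would make the interventions look more harmful than they are. Second, in every arm, a complaint that an intervention did cause but that the participant put down to something else is lost to this item. Blinding the data collector does not help, because the filter is the participant's own judgement. A statistical analysis plan could not repair it either, since the unattributed complaints are never collected by this item.

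**Working it through.** **Plan's own figure.** None exists. The article gives no adverse-effect rate, attribution probability or harm-comparison figure. The only number needed is the arm size, 20 per group (Sample size calculations; 3 × 20 = 60, which agrees with the stated total).

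**Step 1: which listed complaints have another measure?**

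| Listed complaint | Measure without attribution | What remains uncovered |
|---|---|---|
| Neck, back, other muscle or joint pain | Nordic questionnaire, 7-day prevalence, baseline and 4 weeks | Episodes that resolve before the last 7 days: 28 − 7 = 21 days of the period |
| Work productivity | Work Ability Index, baseline and 4 weeks (a related measure) | Little |
| Headache, fatigue, loss of concentration | None named | The whole 4 weeks |

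**Step 2: effect of conditioning on attribution.** Let p be the true proportion with a listed complaint, the same in both arms. Let a_I and a_C be the probabilities that a complaint is attributed to the study in an intervention arm and in control. Then

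- recorded rate in an arm = p × a
- recorded ratio = a_I / a_C, which does not depend on p
- recorded difference = p × (a_I − a_C)
- share of true complaints not recorded = 1 − a

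With equal attribution the ratio is 1 and the difference is 0.

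**Step 3: illustration.** Every p and a below is an assumption; none comes from the article. The last column is the exact probability that a two-sided Fisher test at 0.05 on 20 v 20 would reject although true rates are equal, found by enumerating both binomial distributions.

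| p | a_I / a_C | Recorded rates | Spurious difference | Fisher rejection |
|---|---|---|---|---|
| 20% | 0.5 / 0.5 | 10% v 10% | 0 points | 1.2% |
| 20% | 0.5 / 0.25 | 10% v 5% | 5 points | 1.7% |
| 20% | 0.5 / 0.1 | 10% v 2% | 8 points | 2.9% |
| 20% | 0.8 / 0.1 | 16% v 2% | 14 points | 14.6% |
| 40% | 0.5 / 0.5 | 20% v 20% | 0 points | 2.3% |
| 40% | 0.5 / 0.25 | 20% v 10% | 10 points | 7.2% |
| 40% | 0.5 / 0.1 | 20% v 4% | 16 points | 19.7% |
| 40% | 0.8 / 0.1 | 32% v 4% | 28 points | 56.0% |
| 60% | 0.5 / 0.5 | 30% v 30% | 0 points | 2.5% |
| 60% | 0.5 / 0.25 | 30% v 15% | 15 points | 12.4% |
| 60% | 0.5 / 0.1 | 30% v 6% | 24 points | 39.6% |
| 60% | 0.8 / 0.1 | 48% v 6% | 42 points | 83.5% |

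The Fisher column is only a yardstick for how visible the distortion would be; the article plans no such test. At p = 40% and 0.5 / 0.1, the expected counts are 20 × 0.20 = 4 and 20 × 0.04 = 0.8. Half of the true complaints in the intervention arm go unrecorded (1 − 0.5), as do 90% of those in control (1 − 0.1).

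**Step 4: after the change.** Asking about occurrence regardless of cause sets a = 1 in every arm. With equal true rates the expected difference is then 0 and the ratio 1. The same Fisher yardstick gives 2.3% to 2.4% for p from 20% to 60%.

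**The case against.** The best defence is that the item does what it is meant to do. It is introduced as a record of potential effects of the interventions, and asking participants what they attribute to the study fits that purpose. A reader might infer that the trial plans a between-group harm comparison and that this comparison is biased. The article does not support that: no hypothesis, contrast or test for adverse effects is stated. This stands, and it limits the point to what the item can and cannot support.

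A reader might also infer that controls will hardly ever report anything because they are kept naive. That does not follow. The naivety applies to all three arms, so it does not separate them; receiving no intervention does. Controls also wear the accelerometer and keep a work log, and they believe they are in a workplace health trial, so they have some study involvement to which a complaint could be linked. How far attribution differs is unknown.

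The Nordic questionnaire and the Work Ability Index already give comparisons free of attribution, with a baseline, for part of the list. This stands and narrows the gap, as Step 1 shows. The exclusion of people with a self-reported chronic illness or musculoskeletal condition may lower background rates, and at a 20% true rate most of the assumed scenarios would scarcely show with 20 per arm.

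Finally, the assessment form is not shown, and the article may paraphrase it. If the form already asks occurrence and attribution separately, only the article's description needs correcting. As described, attribution is a condition of being recorded.

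**Conclusion.** The point holds in a limited form. As stated, the item conditions on the participant's attribution, and the control arm has no intervention to attribute a complaint to. The control count is therefore not a usable background rate, the item cannot support an unbiased comparison with control, and unattributed harms are missed in any arm. The consequence falls mainly on headache, fatigue and loss of concentration, and on musculoskeletal complaints that have resolved before the final 7-day window.

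No size can be given from the article. With equal true rates the recorded ratio equals the ratio of attribution probabilities, so the bias is zero if attribution is equal. If controls attribute less, the bias runs towards making the interventions look harmful. The conclusion rests on one judgement, that attribution is likely to differ between arms that receive something and an arm that receives nothing. It does not show that any planned analysis is wrong. It is worth acting on because the remedy is small and the missing data cannot be recovered later.

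**What to change.** At the 4-week follow-up, ask every participant in all three arms whether each listed symptom occurred during the period, whatever its cause. Then ask, as a separate item, whether the participant relates it to the study. Summarise the all-cause counts by arm, with the attributed counts beside them as description. Nothing now collected is lost, because the attribution answer is kept.

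The cost is one change to a form item. More background symptoms will be recorded. Trial status says recruitment had begun but was not complete at submission, so participants who have already finished have answers only to the old item. Report the two versions separately and do not pool them.

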#### Sample size calculations

We did not conduct a formal power analysis to determine sample size, since the threshold for defining harmful levels of sitting is unknown. The proposed sample size of this study is similar to previous pilot studies of workplace sitting and sedentary time. Our sample of 60 participants (three groups of 20 participants) should be sufficient for assessing the direction of intervention effects, while taking into account possible missing data and participation attrition.

#### Randomization and blinding

Participants will be randomly allocated into one of three study groups. A researcher who is not involved in participant recruitment or data collection will produce a randomly generated sequence for allocating participants to one of the three groups. This will be done prior to commencement of the trial. This researcher will prepare consecutively numbered sealed opaque envelopes that contain the group allocation for each individual participant. The envelope for each participant will be opened after the participant has enrolled in the study and after baseline data is collected. The randomization sequence will contain equal numbers of subjects in each group but will be otherwise unrestricted.

Data collection will take place away from the participants’ office and data collectors will be instructed not to enter the office areas of participants. This will ensure blinding of the data collectors to allocation of participants to the sit-stand desk intervention group. The office set-up in the workplace setting for this trial is predominantly private, single occupier offices with few work centers using open-plan office design. This feature of the study setting will assist with limiting the exposure of participants to the other trial interventions and ensure blinding of the data collectors to treatment allocation.

Participants will be kept naive as to the main aim of the study, that is, reduction of unhealthy sitting behaviors. This is because it is believed by the research team that participants being aware that the primary outcome is to reduce sitting behavior might actually change this behavior. Participants will also be blinded where possible to the intervention groups to which they are not allocated. Knowledge of the other interventions that are being tested, both clearly being interventions designed to reduce sitting behavior, might also impact on the sitting behavior of participants. Participants will therefore be informed that they are participating in a trial of general workplace health interventions and remain blinded to the other intervention groups.

A researcher who is blinded to the participant allocation will perform data entry and analysis.

#### Statistical methods

Accelerometer activity counts will be recorded in 1-second intervals and aggregated into 1-minute epochs. We will download ActiGraph data using ActiLife proprietary software and conduct further processing with a custom macro to categorize the data into activity intensity categories: sedentary (<100 counts/minute), light (101 to 2,020 counts/minute), moderate (2,021 to 5,999 counts/minute), and vigorous (≥6,000 counts/minute), based on the frequently used sedentary cut-point for ActiGraph accelerometers
[37] and National Health and Nutrition Examination Survey (NHANES) cut-points for light, moderate, and vigorous intensity levels
[38]. Spurious epochs will be defined as over 20,000 counts/minute
[39], and non-wear time will be defined as periods of consecutive strings of zero-count epochs lasting at least 60 minutes. A whole day of monitoring will be considered as valid if the participant wears the accelerometer for at least 10 hours during their waking time. A workday will be considered valid if the participant wears the accelerometer for at least 75% of their time at work
[40].

We will conduct two-way repeated measures analyses of variance (rANOVA) to compare participants’ objectively assessed time spent in sedentary, light, and moderate-to-vigorous intensity physical activity, as well as their self-reported sitting time, musculoskeletal symptoms, and workability pre- and post-intervention. The two-way rANOVA will have one group factor (education; education plus sit-stand desk; control) and one time factor (pre- and post-intervention). Models will test for group and time main effects and group X time interactions to examine whether any differences in outcome variables vary by study group from pre- to post-intervention.

The primary analysis will be by intention-to-treat. All analyses will be conducted using IBM SPSS Statistics for Windows Version 21.0 (IBM, Armonk, NY, USA).

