
A number of ergonomic interventions have also been investigated as a means of reducing unhealthy sitting behavior or increasing energy expenditure in office workers. These include walking workstations
[23,24], portal pedal machines
[25], and the use of adjustable sit-stand workstations
[11,26]. Of these, adjustable sit-stand desks
[11,26] show particular promise. The sit-stand desk is an adjustable workstation, which attaches to the worker’s desk allowing adjustment of the height of the computer monitor and keyboard allowing work in a sitting or standing position. This device allows the worker to quickly and easily change working position from sitting to standing enabling workers who are seated for long periods of their workday to have frequent standing breaks. There is some evidence that sit-stand desks are effective. A quasi-experimental study
[11] demonstrated reduction in sitting time between 61 and 137 minutes/day when using one of these devices. However, these results have not been replicated in a randomized controlled trial (RCT). To date there has been no investigation of the effect of targeted education (incorporating behavior change) alone, compared with education plus access to an ergonomic device such as an adjustable sit-stand workstation, on reducing sedentary behavior in office-based workers. Although preliminary studies investigating these interventions applied separately have demonstrated promising results
[11,21,23-26], no single intervention appears to suit all workers. It is also possible that education approaches and ergonomic interventions might have complementary effects.

The aim of this study is to determine whether providing office workers an adjustable sit-stand workstation together with targeted education, or targeted education alone leads to changes in sedentary behavior at work compared with no intervention. A secondary aim is to determine if one intervention is more effective than the other in affecting sedentary time.

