#### Primary outcomes

The primary outcomes are the average daily sedentary time during work hours and the average number of breaks per day. These will be measured over a 7-day period immediately prior to randomization and at the completion of the intervention period. Sedentary time will be measured using an accelerometer (ActiGraph GT3XP, ActiGraph, Pensacola, FL, USA) and participants will be required to keep a log of work hours during these measurement periods. Following this period all data will be downloaded and analyzed. The ActiGraph accelerometer is a small, lightweight, plastic device worn around the waist. It measures motion data using three axes. This device is reliable and provides stable measurements of physical activity when compared to other measures of physical activity
[29].

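### The sedentary-time primary outcome grades movement at the waist, not posture, so it may understate the sit-stand desk's effect on sitting by an amount the protocol does not allow us to know

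*Protocol article*

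**What the plan says.** Under Primary outcomes the protocol article states: "The primary outcomes are the average daily sedentary time during work hours and the average number of breaks per day". On the instrument it says: "The ActiGraph accelerometer is a small, lightweight, plastic device worn around the waist. It measures motion data using three axes". The Statistical methods section then describes a macro to "categorize the data into activity intensity categories", the lowest two being "sedentary (<100 counts/minute), light (101 to 2,020 counts/minute". No inclinometer, thigh-worn sensor or other posture rule is described.

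The Background describes the desk as "allowing work in a sitting or standing position". Under Interventions, the desk arm has a matching behavioural target: "Participants will set individual goals for the time that they will spend working in a standing position". Both active arms receive the same education package, which includes self-monitoring of sitting breaks and of daily steps.

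The Randomization and blinding section gives the main aim as reducing unhealthy sitting. The Discussion says that accelerometers and self-report will establish whether sitting changes. Sitting itself is asked about only in two questionnaires, listed under Secondary outcomes and described there as "acceptable self-report measures for assessment of sitting time at work". The only limitation that the Discussion acknowledges is generalizability.

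**The concern.** The trial asks about posture, while its accelerometer outcome records intensity of movement. For the education arm the mismatch may matter less, because extra walking is movement and can cross the cut-point. For the desk arm it bears on the one ingredient that education does not supply, namely working while standing. If some of that standing is still enough to stay under 100 counts/minute, the outcome cannot tell it from sitting.

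The most exposed comparison is desk plus education against education alone, which the Background names as the secondary aim. If it shows no difference, two explanations remain open: the desk adds nothing, or it adds standing that the measure does not register. The Discussion expects the results to inform guidelines and policy on workplace sitting, so the two should not be confused.

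**Working it through.** **Nothing to reproduce.** The Sample size calculations section states that there was no formal power analysis. The article gives no alpha, effect size or standard deviation. The check is of the outcome definition and of how much it could matter.

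**Inputs from the article**
- Cut-point for a sedentary minute: below 100 counts/minute (Statistical methods).
- Placement: waist (Primary outcomes).
- Reduction in sitting reported by a quasi-experimental study of such a device: 61 to 137 min/day (Background).
- Group size: 20 per arm (Sample size calculations).

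**Not in the article, so assumed**
- f, the share of sitting-replacing desk-standing minutes that still fall below 100 counts/minute. It can lie anywhere from 0 to 1.
- The standard deviation of the outcome, taken as 60 to 100 min/day where it is needed.

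**Step 1: direction.** Let S be the minutes per day moved from sitting to desk standing, and W the minutes moved from sitting to activity above the cut-point, such as walking.

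- True reduction in sitting = S + W
- Measured reduction = (1 − f) × S + W
- Shortfall = f × S

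For any f above 0 the desk effect on sitting is understated. If W is similar in the two active arms, it cancels from the contrast between them. What remains is (1 − f) times the difference in S, which is a shift toward no difference.

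**Step 2: size.** Take the case where the whole cited reduction is desk standing (W = 0), so that measured reduction = (1 − f) × true reduction:

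| f | of 61 min/day | of 137 min/day |
|---|---|---|
| 0 | 61 | 137 |
| 0.25 | 0.75 × 61 = 45.8 | 0.75 × 137 = 102.8 |
| 0.5 | 0.5 × 61 = 30.5 | 0.5 × 137 = 68.5 |
| 0.9 | 0.1 × 61 = 6.1 | 0.1 × 137 = 13.7 |

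Setting W = 0 gives the largest loss for a given f. If half of a 61-minute reduction were walking, then at f = 0.5 the measured value would be 0.5 × 30.5 + 30.5 = 45.75 min/day, rather than 30.5.

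**Step 3: effect on the article's own standard.** The sample is said to suffice for judging the direction of effects. For a simple difference of two means with 20 per arm, the standard error is SD × √(2/20) = 0.316 × SD, or 19.0 to 31.6 min/day for SD 60 to 100. The chance that the estimate has the right sign is Φ(measured effect / standard error). For a true 61 min/day and W = 0:

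- f = 0: 61/31.6 = 1.93 to 61/19.0 = 3.21, so 97% to 99.9%
- f = 0.5: 30.5/31.6 = 0.97 to 30.5/19.0 = 1.61, so 83% to 95%
- f = 0.9: 6.1/31.6 = 0.19 to 6.1/19.0 = 0.32, so 58% to 63%

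For a true 137 min/day the chance is still at least 98% at f = 0.5, and 67% to 77% at f = 0.9.

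**Step 4: the other primary outcome.** The article does not say how breaks per day are derived. If they come from the same counts, a change to still standing could go unrecorded as a break. If they come from another source, this problem does not arise.

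**The case against.** The strongest reply is that the size of the problem is unknown. A reader might infer that the desk's effect will be largely missed. That needs f above 0.5 with most of the effect being standing, and the article neither shows nor excludes this. A range for f that starts at 0.5 would build that conclusion into the assumption. At f = 0.25 three quarters of the effect is still seen. The 61 to 137 min/day is also an imperfect anchor: the Background does not say how that study measured sitting, and education-driven walking in the desk arm is recorded normally. These points stand, and they limit the finding to an understatement of unknown size.

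A reader might also infer that the breaks outcome is compromised. The article gives no derivation that would support saying so.

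Second, sitting is measured elsewhere. Two questionnaires are completed at baseline and 4 weeks, analysed in the same repeated measures model, and named in the Discussion alongside the accelerometer. This stands in part: the trial is not blind to a sitting effect. But the questionnaires are secondary, and they are answered by people who know what they received. The article's statement that they correlate with accelerometry does not show that accelerometry detects still standing.

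Third, the cut-point is described as frequently used and the study as a pilot. Frequent use does not show that the rule separates sitting from standing. Pilot status lowers the stakes, but the Discussion still plans conclusions about sitting.

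**Conclusion.** The concern holds in a limited form. As fixed in the article, the sedentary-time outcome cannot separate still standing from sitting, while the desk acts on exactly that distinction. It may understate the desk's effect on sitting and bias the desk-versus-education contrast toward no difference. The amount is unknown and possibly large.

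The direction follows from the definition once some desk standing falls below the cut-point. For the contrast it also assumes that movement-based reductions are similar in the two active arms. The size rests wholly on f and on the share of the effect that is standing, neither of which the article supplies, so the tabulated figures are illustrations and not predictions.

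It would go too far to conclude that the primary outcome should be replaced. Making self-report the sole basis for sitting claims would exchange a possible bias toward no effect for a possible bias toward benefit. Moving the device after recruitment has begun would make later recordings hard to compare with waist-worn baselines already taken.

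**What to change.** - Keep the accelerometer outcome as primary, but label it low-movement time (below 100 counts/minute) at work.
- State before analysis that neither an absence of change in it in the desk arm nor an absence of difference between desk and education will be read as no change in sitting.
- Base every conclusion about sitting on this measure together with the questionnaire sitting time already collected at baseline and 4 weeks, reported side by side.
- State how breaks per day are derived and, if they come from the same counts, apply the same caution.
- If posture can be derived from the three-axis data already recorded, add it as a supporting analysis.

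The wording changes need no new data and no change to procedures in the arms. The price is a more limited conclusion from the primary measure. The questionnaire results also need cautious reading, since reporting bias is possible in the two arms taught about the harms of prolonged sitting.
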